Therefore, the primary objective of this prospective clinical trial is (1) to evaluate the efficacy of P-MCT compared to classical MCT in individuals diagnosed with psychosis, focusing on improvements in positive symptoms (especially delusions), insight, self-esteem, and treatment adherence. Moreover, some specific objectives of this trial include: (2) to validate the ML-based predictive model’s capacity to anticipate MCT treatment response, (3) to evaluate patient satisfaction with P-MCT comparing to classical MCT, integrating both quantitative measures and qualitative insights from focus groups, and (4) to refine the platform’s predictive algorithm through integration of treatment outcome data.

Given that P-MCT has not been previously evaluated and that the ML platform is a novel tool, hypotheses 2–4 are considered exploratory. Our hypotheses are as follows:

H1 - Primary (Comparative efficacy): P-MCT will yield comparable or superior improvements than classical MCT in outcome variables measuring treatment efficacy (positive symptoms, insight, self-esteem, and treatment adherence).H2 - Exploratory (Platform validation): The ML-based predictive model will demonstrate significant predictive capacity to anticipate post-treatment response to MCT on positive symptoms (especially delusions), insight, self-esteem, and treatment adherence, as assessed by the AUC (Area Under the Curve).H3 - Exploratory (Patient satisfaction): Patient satisfaction with P-MCT will be comparable or greater than with classical MCT, as assessed through both quantitative measures and qualitative insights from focus groups.H4 - Exploratory (Platform improvement): The integration of multimodal comprehensive pre-post treatment data from the classical MCT group will refine the machine learning algorithm, resulting in improved predictive accuracy for future patient cohorts.

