#### Comparative efficacy (H1)

2.7.1

To assess the interventions’ efficacy, improvements in the proximal targets of MCT, as defined in recent meta-analyses and meta-reviews (11, 12), will be analyzed using statistical methods (43). These targets include global positive symptoms, including delusions, cognitive insight, self-esteem and treatment adherence. Regression models for repeated measures will be used for each proximal target, with the treatment group (P-MCT or classical MCT) included as a covariate for comparison. Additionally, mean differences between baseline and post-treatment scores in each group will be compared using Student’s t-tests, or Mann-Whitney tests if the assumption of normality is violated. Missing data will be handled using multiple imputation techniques. Subgroup analyses will be conducted based on sex, age, and baseline symptom severity. Sensitivity analyses will assess robustness of findings. ANCOVAs will explore whether responses differ across participant profiles (44), with treatment as the independent variable and composite participant profiles as a fixed factor. Covariates will include number of sessions attended, online vs. face-to-face delivery, and session frequency. Participant profiles will be identified using unsupervised ML techniques.

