#### Platform validation (H2)

2.7.2

In the classical MCT group, the predictive accuracy of the platform will be evaluated by comparing actual results with predictions in the five key variables (positive symptoms, delusions, insight, self-esteem, and treatment completion), with predictive performance assessed using the AUC for classification models (45) and RMSE and the R^2^ determination coefficient for regression models (46). In the P-MCT group, the analysis will focus on whether this approach led to improved outcomes compared to baseline predictions. Effect sizes will be calculated using Cohen’s d.

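### The exploratory profile ANCOVAs adjust a randomised comparison for sessions attended, a post-randomisation variable that P-MCT may itself change

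*Protocol article*

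**What the plan says.** All of the following is in the protocol article.

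- **Main H1 models (2.7.1).** The sentence that sets up these models begins: "Regression models for repeated measures will be used for each proximal target, with the treatment group (P-MCT or classical MCT) included as a covariate for". Its stated purpose is to contrast the arms. Baseline-to-post changes are also compared by t-test or Mann-Whitney test. No attendance covariate is named for either.
- **Profile analysis (2.7.1).** "ANCOVAs will explore whether responses differ across participant profiles (44), with treatment as the independent variable and composite participant profiles as a fixed factor". The next sentence is: "Covariates will include number of sessions attended, online vs. face-to-face delivery, and session frequency".
- **Outcomes (2.7.1).** "These targets include global positive symptoms, including delusions, cognitive insight, self-esteem and treatment adherence". The Introduction states H1 as: "P-MCT will yield comparable or superior improvements than classical MCT in outcome variables measuring treatment efficacy (positive symptoms, insight, self-esteem, and treatment adherence". Section 2.7.2 lists the "five key variables (positive symptoms, delusions, insight, self-esteem, and treatment completion", so its counterpart to adherence is completion of treatment.
- **Timing (2.1 and 2.5).** Randomisation follows the baseline assessment and precedes treatment. Attendance is recorded by questionnaire after each session attended.
- **Homework (2.5).** The arms differ only in homework. Treatment adherence is one of the domains that has its own set of P-MCT exercises.
- **Other covariates (2.5).** Delivery format and session frequency vary by centre with staff resources and are to be used as covariables. Attendance is not mentioned there.

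**The concern.** A treatment contrast keeps its randomised interpretation when it is adjusted for variables fixed before allocation. Sessions attended is not such a variable. Conditioning on it can do three things:

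- remove whatever part of a P-MCT benefit works through better attendance;
- open a non-causal path between arm and outcome through unmeasured causes of both attendance and outcome, such as motivation or severity;
- bring the outcome process itself into the covariate, since 2.5 allows the intervention to be discontinued when symptoms worsen, so a poor course can shorten attendance.

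The design gives a plausible route from arm to attendance, because some P-MCT homework is aimed at adherence and H1 allows for superior adherence. At stake are the treatment and treatment-by-profile estimates of the ANCOVAs. In a trial of personalisation, readers will look at these when asking who benefits.

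**Working it through.** **1. Is attendance post-randomisation?** Yes: 2.1 places randomisation after baseline and before the sessions, and 2.5 records attendance session by session.

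**2. Which model contains it?** The covariate sentence directly follows the ANCOVA sentence and most naturally belongs to it. The repeated-measures and t-test sentences do not name it.

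**3. Size of the shift in SD units.** The plan states no figure for this, so every input below is assumed. Let T be the arm, U an unmeasured common cause, S attendance and Y the outcome (higher is better), with S scaled to unit variance within arm:

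- S = a·T + c·U + error
- Y = d·T + b·S + g·U + error

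The randomised (total) effect is d + a·b. Given S and T, the mean of U is c·(S − a·T), so the coefficient of T adjusted for S is d − a·c·g. The shift is therefore

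(d − a·c·g) − (d + a·b) = −a·(b + c·g).

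Taking a total effect of 0.50 SD for illustration (a simulation with N = 1,000,000 agreed with the formula):

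| a | b | c = g | shift | adjusted estimate |
|---|---|---|---|---|
| 0 | any | any | 0 | 0.50 |
| 0.2 | 0 | 0.5 | −0.2 × 0.25 = −0.05 | 0.45 |
| 0.2 | 0.3 | 0 | −0.2 × 0.30 = −0.06 | 0.44 |
| 0.2 | 0.3 | 0.5 | −0.2 × 0.55 = −0.11 | 0.39 |
| 0.4 | 0 | 0.5 | −0.4 × 0.25 = −0.10 | 0.40 |
| 0.4 | 0.3 | 0 | −0.4 × 0.30 = −0.12 | 0.38 |
| 0.4 | 0.3 | 0.5 | −0.4 × 0.55 = −0.22 | 0.28 |

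If P-MCT lowered attendance (a < 0), the sign would reverse, so the direction is not fixed either.

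**4. The same on the session scale.** Assume sessions = 7 + δ·T + 1.5·U + noise with SD σ, clipped to 0–10, and an outcome that rises 0.3 SD per SD of U. With no true effect and ignoring clipping, the shift is −δ × 0.3 × 1.5 / (1.5² + σ²):

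- δ = 1: −0.45/3.25 = −0.138 at σ = 1; −0.45/4.5 = −0.100 at σ = 1.5; −0.45/6.25 = −0.072 at σ = 2. Simulation with clipping (202 patients, 2,000 trials) gives −0.135, −0.09 and −0.067.
- δ = 0.5, σ = 1.5: simulation gives −0.05.
- δ = 0.25: a quarter of the δ = 1 values, about −0.035 to −0.018 unclipped; simulation gives −0.02 to −0.03.
- δ = 0: no shift.

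Now add a direct effect of 0.3 SD and a gain of 0.1 SD per session attended. The total against the adjusted estimate is then 0.39 against 0.20 for δ = 1 and 0.34 against 0.25 for δ = 0.5 (both at σ = 1.5), and about 0.32 against 0.27–0.28 for δ = 0.25.

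**5. Treatment-by-profile contrasts.** By the same formula, with common b, c and g, the difference in treatment effect between two profiles shifts by −(a₁ − a₂)·(b + c·g), where a₁ and a₂ are the arm effects on attendance in each profile. It is distorted if P-MCT changes attendance more in one profile than in the other, and otherwise not by this route.

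**The case against.** The strongest reply is about reach. The H1 comparison is assigned to the repeated-measures regressions and the simple tests, and neither is stated to adjust for attendance. The ANCOVAs are described as exploratory. This stands: a reader might infer that the primary P-MCT effect is biased, but the text does not support that. The covariate sentence does not name its model, however, so the protocol should rule out wider use.

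Second, bias is not certain. The group sessions are identical, patients are blinded, homework covers only the three domains with the lowest predicted improvement, and H1 accepts comparable adherence. With no arm effect on attendance the main-effect shift is zero. This also stands. But a trial that lists adherence among its outcomes and writes exercises for it cannot assume in advance that attendance is unaffected.

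Third, the numbers rest on assumed inputs. One extra session is about 0.45 to 0.6 SD of attendance in that simulation, a large effect for homework alone. The sampling SD of the coefficient is about 0.145, so even the one-session null shift (0.067 to 0.135) is below one standard error. That is fair as to size, although this bias does not shrink as the sample grows.

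Two further inferences are not supported. The adjustment is close to circular only if an ANCOVA is run with adherence as the outcome. Section 2.7.1 neither says nor excludes this, and the adherence instrument is in a supplement that is not shown. Nor does the list show that baseline scores are left out, since it need not be exhaustive.

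**Conclusion.** The point holds for the exploratory profile ANCOVAs. As written, they condition a randomised contrast on a variable that arises after allocation and that the experimental arm may influence. If P-MCT changes attendance, and attendance is linked to the outcome directly or through a common cause, their treatment estimates do not estimate the randomised effect. The treatment-by-profile estimates may be affected too.

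The size cannot be fixed from the documents. It runs from zero, through about −0.02 to −0.03 SD (a quarter of a session) to about −0.07 to −0.14 SD (one session) in the null case, and is larger if attendance itself improves the outcome. A reader might take the loss of roughly half the effect (0.39 reported as 0.20) as the expected result. It is one assumed scenario.

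Severity is moderate: a definite specification error with a simple remedy, in a model that is not the main H1 analysis.

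**What to change.** In 2.7.1:

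- strike attendance from the covariate sentence and name the model to which the sentence applies;
- keep delivery format and session frequency, which 2.5 describes as set by centre;
- add that no between-arm model adjusts for the number of sessions attended;
- if the role of attendance is of interest, report it only in a separately labelled secondary dose-response, mediation or complier-type analysis.

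The cost is a sentence or two. No new data are needed and the sample size does not change. The change should be made before any unblinded analysis.

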#### Platform validation (H2)

2.7.2

In the classical MCT group, the predictive accuracy of the platform will be evaluated by comparing actual results with predictions in the five key variables (positive symptoms, delusions, insight, self-esteem, and treatment completion), with predictive performance assessed using the AUC for classification models (45) and RMSE and the R^2^ determination coefficient for regression models (46). In the P-MCT group, the analysis will focus on whether this approach led to improved outcomes compared to baseline predictions. Effect sizes will be calculated using Cohen’s d.

#### Patient satisfaction (H3)

2.7.3

Patient satisfaction will be assessed using a mixed-methods approach, combining quantitative measures collected post-treatment and at follow-up with qualitative data from focus groups conducted at each center. Focus groups will be transcribed verbatim, coded and analyzed using content analysis using ATLAS.ti, and grouped into categories and subcategories reflecting recurrent themes (satisfaction, perceived benefits, and barriers). Methodological rigor will follow Guba and Lincoln’s criteria of dependability, credibility, transferability, and confirmability (47). Triangulation across researchers and sites will be performed in monthly consortium meetings to enhance reliability and credibility. Representative quotes will be reported while maintaining anonymity.

#### Platform improvement (H4)

2.7.4

Exploratory analyses using unsupervised ML techniques will examine whether integration of comprehensive pre-post distal treatment data, including quantitative clinical, cognitive, psychological measures and blood biomarker data (e.g., depression, trauma, cognitive bias, SP1/SP4 expression), can refine the ML platform and improve predictive accuracy for future patient cohorts. Qualitative data will not be used for platform improvement.

This combined approach allows for integration of quantitative outcomes with qualitative insights, providing a comprehensive assessment of intervention efficacy and patient experiences across the five participating countries.

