### Measures

2.3

Data will be collected on sociodemographic, clinical, cognitive (neurocognitive, metacognitive, social-cognitive), and psychological variables. Given the transnational nature of the study, official validated translations of all instruments were used for each participating country. When validated translations existed but item ordering differed between countries, administration was standardized according to the official English version to ensure consistency across sites. For instruments lacking official translations in some specific languages (e.g., The Internal, Personal, and Situational Attributions Questionnaire (IPSAQ), Fish Task) and for consortium-developed scales (e.g., modified Patient-Reported Impact of Symptoms in Schizophrenia (PRISS) scale to monitor symptoms during treatment, satisfaction with MCT treatment), forward-backward translation procedures were conducted by independent bilingual researchers to ensure semantic and conceptual equivalence. The instruments used and their characteristics are presented in **Supplementary Table S1**.

Blood samples will be drawn from participants at baseline and post-treatment. In both centers collecting blood samples (FSJD and UV), leukocyte subpopulation counts obtained from blood count analyses and C-reactive protein levels will be collected. At the FSJD site, peripheral expression levels of SP transcription factors (SP1 and SP4) will be analyzed as part of a subproject aimed at identifying biomarkers with transcriptional reprogramming capacity involved in the response to MCT. Biomarkers are included because they provide objective biological indicators of inflammatory and transcriptional processes that may influence cognitive functioning and symptom severity in psychosis. These processes are increasingly recognized as moderators of treatment response in psychological interventions. Including biomarkers enables subgroup analyses to determine whether MCT efficacy varies by biological profile.

Incorporating biomarker data will refine the ML algorithm. This iterative process will determine which biomarkers consistently improve predictive accuracy, guiding future versions of the platform toward more biologically informed personalization.

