A key strategic decision concerned how to personalize homework. Rather than reinforcing domains predicted to improve most, the consortium adopted a recovery-oriented approach by targeting the three outcome domains with the lowest predicted improvement out of the five domains discussed to best represent successful treatment response (positive symptoms, insight, self-esteem, and treatment adherence). personalized exercises were developed by clinicians within the consortium using (1) clinical practice guidelines and (2) predictive features identified using SHAP values from the ML model (39), ensuring alignment between clinical relevance and data-driven indicators. Sixteen exercises (four per outcome domain) were developed and standardized in length and complexity to ensure that any differences in treatment effects arise from personalization rather than workload. Homework assignment follows a fixed and reproducible rule: for each participant, the platform identifies the three outcome domains with the lowest predicted improvement. Across the ten MCT sessions, homework is assigned by cycling repeatedly through these three domains (Domain 1 → Domain 2 → Domain 3 → repeat). Because the program includes ten sessions, Domain 1 receives four exercises, while Domains 2 and 3 each receive three exercises. Within each domain, exercises are delivered sequentially (Exercise 1 to Exercise 4), ensuring a consistent rotation structure tailored to the participant’s predicted needs while maintaining standardization of the overall intervention. The established order of tasks represents the degree of relevance of the related factor detected by the ML model. For instance, in the Positive Symptom analysis, related factors associated with improvement in positive symptoms included positive symptoms themselves, negative symptoms, JTC and self-reflection, in this order. As a result, in order to target positive symptoms, the four homework tasks related to this domain include (1) psychoeducation on positive symptoms, (2) an activity planner to reduce negative symptoms, (3) a task to identify and correct JTC biases, combining self-reflection with JTC improvement, and (4) positive symptoms psychoeducation on stress management.

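### H4 names only unsupervised learning for a predictive-accuracy aim, and the claim about which biomarkers improve accuracy is too strong for one- and two-site samples

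*Protocol article*

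**What the plan says.** The H4 hypothesis in the Introduction reads: "The integration of multimodal comprehensive pre-post treatment data from the classical MCT group will refine the machine learning algorithm", with better accuracy for later cohorts as the expected result. Section 2.7.4 gives the method: "Exploratory analyses using unsupervised ML techniques will examine whether integration of comprehensive pre-post distal treatment data", extended to cognitive, psychological and blood data, "can refine the ML platform and improve predictive accuracy for future patient cohorts". No other technique is named for H4.

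Section 2.5 says that results from the classical MCT condition are kept solely to confirm how accurate the platform's predictions are.

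On biomarkers, section 2.3 says: "In both centers collecting blood samples (FSJD and UV), leukocyte subpopulation counts obtained from blood count analyses and C-reactive protein levels will be collected". It adds: "At the FSJD site, peripheral expression levels of SP transcription factors (SP1 and SP4) will be analyzed". It then concludes: "This iterative process will determine which biomarkers consistently improve predictive accuracy".

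For H2, section 2.7.2 compares predictions with actual results in the classical arm, "with predictive performance assessed using the AUC for classification models (45) and RMSE" and R-squared for regression models. No comparator model is named. Section 2.5 gives an example of what drives one prediction: "in the Positive Symptom analysis, related factors associated with improvement in positive symptoms included positive symptoms themselves", listed first.

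The Introduction labels H2 to H4 exploratory.

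**The concern.** Predictive accuracy is agreement between predicted and observed outcomes. Clustering and dimension reduction are fitted without an outcome, so an analysis that followed section 2.7.4 literally would produce profiles or components and leave H4 unanswered. The article uses the term correctly elsewhere: section 2.7.1 assigns unsupervised learning to finding participant profiles, and section 2.7.2 gives accuracy metrics, but for H2 only. The mismatch is therefore in what section 2.7.4 states and is more than a missing detail.

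Two further statements add to it. Section 2.5 restricts the classical-arm results to confirming accuracy, while the Introduction uses classical-arm data to refine the algorithm. Section 2.3 makes a definite promise about biomarkers that are measured at one or two of five sites.

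At stake is a reported improvement in the platform, or a list of useful biomarkers, that the analysis did not measure or measured too imprecisely to carry forward. The Discussion looks ahead to medical-device certification, so such a statement would be used.

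**Working it through.** **1. Plan's own figure.** The only sample-size calculation (section 2.6) uses d = 0.5, 95% power and two-sided testing. With alpha 0.05 (assumed, not stated), the t-test needs 104.93, so 105 per arm and 210 in total, as stated. It concerns total PANSS. The article gives no number for the biomarker, H2 or H4 analyses, so these are derived below.

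**2. Inputs.** 51 patients per center (Abstract; a minimum in section 2.2); equal arms and 20% loss (section 2.6); SP1/SP4 at one site, CRP and leukocytes at two (section 2.3); H4 uses the classical arm (Introduction).

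**3. Patients available, classical arm.**
- SP1/SP4: 51/2 = 25.5, about 25; × 0.8 = 20.4, about 20.
- CRP and leukocytes: 2 × 51 = 102; 102/2 = 51; × 0.8 = 40.8, about 41.
- Clinical, cognitive and psychological data: 255/2 = 127.5, about 127; × 0.8 = 102.

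**4. Smallest correlation detectable with 80% power, two-sided 5% (Fisher z).** r = tanh[(1.96 + 0.8416)/√(n − 3)].
- n = 20: tanh(2.8016/√17) = tanh(0.679) = 0.59. n = 25: 0.54.
- n = 41: tanh(2.8016/√38) = tanh(0.454) = 0.43. n = 51: 0.38.

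If the SP1/SP4 site enrolled twice the minimum (102), it would have about 41 classical-arm completers and reach 0.43. Blood sampling needs a separate consent (section 4), which could lower these counts.

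**5. Precision of an AUC of 0.70 (Hanley-McNeil, half responders assumed).** The 95% half-width is 0.23 at n = 20, 0.16 at n = 41 and 0.10 at n = 102. These are for a single AUC; a paired difference has its own standard error.

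**6. H4 statements side by side.** Aim: better accuracy. Named method: unsupervised. Named accuracy metric, supervised refit or test data for the refined model: none. Use of the classical arm: refinement (Introduction) against confirmation only (section 2.5).

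**7. What the baseline score alone would give for H2.** Assume bivariate normal scores, equal SDs, response defined as above-median improvement, and pre-post correlation r of 0.5 to 0.7 (none of this is in the article).
- Correlation of baseline with change: c = √((1 − r)/2), so 0.50 at r = 0.5 and 0.39 at r = 0.7. The R-squared for change is c², 0.25 and 0.15.
- AUC = 1/2 + (2/π) arcsin(c/√2): 0.73 at r = 0.5, 0.705 at r = 0.6, 0.677 (about 0.68) at r = 0.7. Simulation agrees to within 0.002.
- With 102 completers (51 responders, 51 not), an AUC of 0.677 has a half-width of about 0.104, so its lower limit is 0.677 − 0.104 = 0.573. The baseline score alone would then be significantly better than 0.5.

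**The case against.** The strongest reply is that unsupervised learning has a legitimate place here. The Discussion says that predictions rest on composite patient profiles, so new profiles could feed the existing predictor, with accuracy measured as in section 2.7.2. H2 to H4 are exploratory, the Discussion speaks only of preliminary biological insights, and validation details normally sit in an analysis plan that is not shown.

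Part of this stands. Missing detail on data splits is not in itself a fault of an article. But section 2.7.4 positively names a method, and that method cannot deliver the stated result without a supervised step. The exploratory label also sits badly with the definite wording in section 2.3.

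On the two uses of the classical arm, the sentence in section 2.5 could be read as covering only the platform's output. That narrows the conflict, but the text should say so.

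Several stronger readings are tempting and not supported:
- A reader might infer that variables will be chosen and judged on the same patients. No section says this.
- A reader might infer that post-treatment values will be inputs for untreated patients. Objective 4 in the Introduction speaks of integrating outcome data, so they may serve as outcomes for retraining.
- A reader might conclude that H2 cannot support its claim. Comparing predictions made at baseline with later results in new patients, by AUC, RMSE and R-squared, is valid prospective validation. H2 claims predictive capacity, not gain over baseline. A fixed model's R-squared in new patients can also be low or negative, so a favourable value is not automatic.
- A reader might take about 25 patients as the basis for all biomarkers, or for H4 as a whole. It applies to SP1/SP4 only.
- The baseline-score argument does not extend to treatment completion, which is not a change score.

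**Conclusion.** The concern holds for H4 and for the biomarker claim. As written, section 2.7.4 would leave H4 unanswered, because the only named method yields no accuracy, and no held-out test of the refined model is named. The roles given to the classical-arm data in the Introduction and section 2.5 conflict as worded and need reconciling.

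The claim in section 2.3 is too strong. With about 20 classical-arm completers, only an SP1/SP4 correlation near 0.59 is reliably detectable, and a single site cannot show consistency across sites. For CRP and leukocytes the figure is about 0.43 with about 41 completers. These sizes assume 51 enrolled per site, equal arms, 20% loss and blood from every participant.

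For H2 the point is an improvement and does not invalidate the planned analysis. Under the assumed correlations of 0.5 to 0.7, an AUC of about 0.73 to 0.68 could come from the baseline score alone, so the planned metrics show accuracy but not what the platform adds. None of this affects the H1 comparison.

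**What to change.** **H4 (section 2.7.4).** State that the refined models are supervised and use baseline inputs only, with post-treatment values as outcomes. Keep all variable selection inside cross-validation. Compare the refined models with the stored platform predictions on the same classical-MCT patients. Unsupervised profiles may be candidate features.

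**Biomarkers (section 2.3).** Report SP1/SP4, CRP and leukocytes as exploratory associations with confidence intervals, and soften the sentence to say that the trial may suggest candidates for later testing.

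**Classical-arm data (Introduction and section 2.5).** Reconcile the two statements: say that the predictions are first used to assess the existing platform, and that the same arm's data then serve H4.

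**H2 (section 2.7.2).** For the change-score outcomes, not treatment completion, also report the gain in AUC and R-squared, with a confidence interval, over a model that uses only the baseline value of that outcome.

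The cost is revised wording and modest extra analysis. No new data are needed, since predictions are already recorded for both arms (section 2.1). The downside is a less favourable headline accuracy.
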